### 4.2. Experimental Phase

This phase includes 5 face-to-face visits. Except for visit 1, these visits are conditioned by the patients’ chemotherapy treatment sessions and are carried out in the following 4–7 days after their infusion, a period during which there is greater toxicity and taste affectation.

#### 4.2.1. Visit 1 (v1)

Once it is verified that patients meet the inclusion and exclusion criteria, the experimental phase’s first visit will be made. In this visit, the patient is randomized, and the following initial measures are taken:Health study (blood pressure and heart rate);Morphofunctional assessment:
▪Anthropometric measurements;▪Electrical bioimpedance;▪Dynamometry;▪Nutritional ultrasound;▪Up and Go Test.Sniffin’ Stick Smell Test;Collection and measurement of saliva volume;Blood sample extraction coinciding with the prechemotherapy analysis:▪Biochemical parameters;▪Plasma metabolomic analysis;▪Plasma cytokine profile;▪Fatty acids from the erythrocyte membrane;▪Enzymatic antioxidant defense system in erythrocytes;▪Body oxidative stress in urine;▪Fecal microbiota and metagenome;▪Saliva microbiota and metagenome.

During this visit, the following documentation is collected:Daily Food Record (3 days per holiday);Food consumption frequency;International Physical Activity Questionnaire;Quality of life questionnaire;Feces sample;Urine sample.

Once the tests have been carried out, the patient will be instructed on the following:Nutritional treatment. If an oral nutritional supplement is needed, a polymeric, hypercaloric, and hyperproteic formula enriched in omega-3 fatty acids is prescribed depending on their energy requirements;Healthy eating guidelines for cancer patients using the book “Cooking with Science Against Cancer” as a support are given to the patient;Physical exercise guidelines.

During this visit, the study treatment (Miraculin-based food supplement or placebo) is delivered to the patient based on randomization, and the following documentation is delivered to bring the next visit (v2):Product efficacy satisfaction questionnaire (prechemotherapy);Next face-to-face visit date.

The following documentation will also be delivered to bring on the third visit (v3):Product consumption control daily sheet;Product consumption tolerance record sheet;Record sheet of adverse effects.

#### 4.2.2. Visit 2 (v2)

Carried out 4–7 days after the chemotherapy session, during this visit, the following measurements will be made:
Anthropometric measurements;Electrogustometry;Smell and taste tests:▪Taste Strips Test;▪Sniffin ‘Sticks Smell Test.Collection and measurement of saliva volume;Taste and Smell Modified Survey;Product Efficacy Satisfaction Questionnaire (Post Chemotherapy).

The following behavioral reinforcements are also carried out on this visit:Nutritional treatment and physical activity;Consumption and registration of the assigned treatment;Tolerance and adverse effects registry.

At the end of this visit, the following documentation and material are given to the patient. These have to be delivered on the next visit (v3):Daily Food Record (3 days per holiday);International Physical Activity Questionnaire;Quality of Life Questionnaire;Blood sample extraction appointment;Feces container;Urine container.

#### 4.2.3. Visit 3 (v3)

This visit will take place ±1 month after visit 1 (v1) and 3–4 days after the patient’s chemotherapy treatment session. This visit is similar to visit 1. A detailed version of the performed assessments is included in the Supplementary Material (File S4).

#### 4.2.4. Visit 4 (v4)

This visit will take place ±2 months after visit 1 (v1) and 3–4 days after the patient’s chemotherapy treatment session. This visit is similar to visit 1. A detailed version of the assessments performed is included in the Supplementary Material (File S4). 

#### 4.2.5. Visit 5 (v5)

This visit will take place ±3 months after visit 1 (v1) and 3–4 days after the patient’s chemotherapy treatment session. This visit is similar to visit 1. A detailed version of the assessments performed is included in the Supplementary Material (File S4). 

## 5. General Characteristics of the Population

This section presents very preliminary results of the clinical trial. For the present study a total of 62 patients were evaluated for eligibility. Of them, 31 met the selection criteria and were randomized into three intervention groups (Figure 5). During follow-up, there were 10 dropouts, mainly due to the consumption of the supplement distorted the taste of some non-sweet acidic foods (n = 6) and because of the prescription added difficulty to their, already complex, antineoplastic treatment (n = 2). A final sample of 21 patients completed the clinical trial.

The sample was made up of 61.9% women and 38.1% men with a mean age of 59.8 ± 11.65 years old, all of them undergoing active treatment with chemotherapy and taste alteration measured by electrogustometry (Table 3). The average body mass index was 22.37 ± 3.67 kg/m^2^, classifying the patients as normal weight. However, the weight lost in the last 3 months was −7.60 ± 5.76%, with no significant differences between treatment groups. 

The most prevalent type of cancer was colorectal cancer (28.6%) followed by breast, lung, pancreas and liver cancers, each with 9.5%. Fasting glycemic control (105 ± 19 mg/dL) was within the normal reference parameters (74–106 mg/dL). The insulin concentration (12 ± 10 µU/mL) was normal in the entire population (3–25 µU/mL) as well as the lipid profile. All patients had systemic inflammation (CRP > 5 mg/dL). Both vitamins and minerals were found within the reference values except for vitamin D, which means blood concentration (21.25 ± 13.86 ng/mL) was insufficient (range 15–30 ng/mL).

## 6. Expected Results

To the best of the authors’ knowledge, this is the first clinical trial conducted to examine the effects of regular consumption of the miraculin-based food supplement, containing the miracle fruit extract DMB, on taste perception and nutritional status in malnourished cancer patients undergoing active antineoplastic treatment. Nonetheless, a double-blind, placebo-controlled, randomized controlled trial to evaluate a miracle berry supplement on taste alteration is also being carried out at the moment. However, this clinical trial is carried out exclusively in head and neck cancer treated with radiotherapy and subjectively assessing the disorder taste [168]. In our trial, we used a triple-blind randomized approach. The present study uses a freeze-dried extract from the fruits of *Synsepalum dulcificum*, approved as a novel food and considered safe for human consumption in Europe by EFSA [70]. Orally dissolving tablets rich in miraculin, a glycoprotein with the ability to change the taste perception of sour foods to a sweet taste [169], are used to improve taste perception in cancer patients.

Taste and smell disorders are common in patients with cancer in active antineoplastic treatment; taste disturbance prevalence ranges from approximately 20 to 86% [31] and persists throughout the treatment [32], while smell disorders are approximately 5 to 60% in cancer patients undergoing chemotherapy [4]. In this sense, cancer patients with taste and smell disorders develop food aversions that reduce food intake and promote poor nutrition, deteriorate quality of life [5,29] and increase the risk of malnutrition [27,28,170]. Poor nutritional status is related to an increase in complications and toxicity of treatment, interruption or failure of treatments, longer hospital stays, readmissions, and infections and is responsible for up to 10–20% of the mortality of oncologic patients [171].

This is the first study carried out with the novel miraculin-based novel food ingredient DMB, contained in the miraculin-based food supplement, that objectively assesses taste perception in cancer patients undergoing active antineoplastic treatment through electrogustometry. In this sense, electrical taste evaluation provides an accurate means for quantitatively assessing the taste system [24], and although electrical stimulation seems to activate the same brain regions as chemical stimulation [25] and has high test-retest reliability [172], to complete taste perception assessment in cancer patients, a chemical assessment of taste has been performed. Taste and smell senses are closely related to food taste perception [173]. Taking this into account, the orthonasal olfactory function of malnourished cancer patients in active antineoplastic treatment will also be evaluated in the present study.

The main expected effect is that malnourished cancer patients with taste distortion and consuming the miraculin-based food supplement improve their food taste perception and promote better food intake, improving malnutrition and associated risks.

Some studies have shown the effect of *Synsepalum dulcificum* fruit for treating taste disorders in cancer patients undergoing chemotherapy. A pilot clinical trial in cancer patients with dysgeusia revealed that the consumption was safe, patients showed a taste improvement and, when taste stabilization was considered, the improvement rate was higher [21]. Later, a pilot crossover clinical trial demonstrated improvements in taste disorders; some patients increased food intake, and some reported metallic taste disappearance [22]. Both studies, however, had a short duration, making it impossible to evaluate their impact on the nutritional status of the patients. Other drawbacks are their designs, which were unblinded, and the lack of validated tools to assess changes in taste. However, these pilot clinical trials have set a precedent for miracle fruit use in taste disorders in patients with dysgeusia due to antineoplastic treatment.

Malnutrition is highly prevalent in cancer patients, and up to 10–20% of cancer patients may die because of malnutrition rather than the tumor [43]. Therefore, its early identification is vital in early treatment. This clinical trial is based on the new criteria for the diagnosis of malnutrition, which includes the assessment of phenotypic criteria (nonvolitional weight loss, low BMI, reduced muscle mass) and etiological criteria (reduced food intake or assimilation, disease burden/inflammation presence) [23]. The diagnosis of malnutrition includes at least one phenotypic and one etiological criterion. Malnutrition severity is given by the phenotypic criteria presented, while the etiologic criteria are used to provide the context to guide the nutritional intervention and anticipated outcomes. In this sense, morphofunctional assessment has been used to support malnutrition diagnosis. This new assessment tool includes classic parameters (anthropometric parameters, biochemical parameters, food intake) and emerging parameters (bioelectrical impedance, nutritional ultrasound, dynamometry, functional test, biochemical parameters) [44] that allow an accurate approximation of the nutritional status of a patient. This evaluation includes functional assessments such as hand-grip strength or TUG used as a supportive measure of malnutrition diagnosis [23].

The parameters that the morphofunctional assessment incorporates are expected to improve after the regular consumption of the miraculin-based food supplement since a change in the patient’s nutritional status will have a positive impact on them.

Taste and smell disorders are common in patients undergoing antineoplastic treatments, reducing not only their food intake but also their quality of life [174,175]. Moreover, malnutrition by itself negatively impacts the quality of life and oncologic treatment. Sour and salty tastes seem to be the tastes that are most affected by antineoplastic treatments [176]. In this sense, it is expected that the regular consumption of the miraculin-based food supplement improves the acid food taste perception and helps to improve the quality of life of patients.

In addition to miraculin, miracle berry contains a large amount of antioxidants. Indeed, it is rich in terpenoids (74.4%), phenolic compounds (15.8%), and flavonoids (11.9%) and exhibits a high antioxidant activity (18.9%) [177]. It also has anticancer abilities due to the different amides existing in the miracle fruit [178]. In cancer, high oxidative stress and profound alterations of the antioxidant defense system occur [101,102,103,104], partly associated with the inflammatory state [102] and partly related to the altered nutritional status affecting key molecules in the maintenance of oxidative homeostasis such as retinol, beta-carotene, vitamin E, vitamin C, increased ratio of oxidized to reduced glutathione, etc. [100,103,113,114]. Consequently, it is expected that the administration of DMB will contribute to decreasing the degree of oxidative stress, as evaluated in the present study through the urinary excretion of the biomarkers F2-alpha-isoprostanes and 8-hydroxy-deoxy-deoxy-guanosine [154,155,179,180]. Likewise, an improvement in both nonenzymatic and enzymatic antioxidant defense status [115] is expected, mainly based on the improvement in food intake and nutritional status of the treated patients.

Inflammation is a constant in cancer. As previously indicated, in addition to the production of proinflammatory cytokines and acute phase reactant proteins, tumor cells produce specific cytokines such as LIF and PIF, among others [95,96,97,98]. In the present project, it is expected that the improvement in nutritional status will contribute decisively to the reduction in the inflammatory process associated with cancer and, therefore, to a reduction in both proinflammatory cytokines and cancer-induced secretion factors themselves. Likewise, an increase in anti-inflammatory cytokines such as IL-4 and IL-10, which are decreased in tumor processes [95,96], would presumably occur.

As has been indicated before, malnutrition usually affects cancer patients. Beyond changes in the plasma proteome, this state of malnutrition causes changes in numerous low molecular weight biomarkers, many of which are derived from cellular metabolic activity, such as intermediary metabolism compounds, amino acids and amino acid derivatives, and compounds largely derived from nutrients and bioactive compounds derived from food intake [116,117]. The improvement of the latter and nutritional status should be associated with a metabolome closer to that of the healthy subject. In the present project, the study of the metabolome of compounds of molecular weight lower than 500 Da, as well as the lipidomic analysis, especially of lipid species (mono acyl, diacyl, and triacylglycerols, phospholipids, acylcarnitine derivatives, and oxylipins) [160,161,162], will allow us to know to what extent the miraculin supplementation translates into the improvement of the plasma metabolome in cancer subjects through the improvement of the nutritional status of the patients. On the other hand, it can be hypothesized that a higher and better quality food intake will be translated into higher intakes of essential fatty acids that should result in an improvement in the status of long-chain polyunsaturated fatty acids [91,92,93]. In this work, we plan to determine the status of essential fatty acids and their polyunsaturated derivatives by determining the fatty acid profile of the erythrocyte membrane [153]; given that supplementation with miraculin is extended for 12 weeks, this time is sufficient for the total pool of erythrocytes to be completely renewed, and therefore any change in the fatty acid profile would be indicative of improved nutritional status.

Numerous studies carried out in recent years using metagenomic techniques indicate that diet is a powerful agent involved in the establishment of specific microbiota, both in the oral cavity and in the colon [167]. In the present study, we addressed changes in the saliva and stool microbiota in cancer patients. Treatment with DMB and the increase in salivation related to some of its active compounds, such as some amides, as well as the change induced in food intake as a consequence of the improvement of taste and smell alterations, should result in relevant changes both in the salivary microbiome, which should be closer to that of the healthy subject, and in the bacterial pattern of the feces, indicative of the microbiome of the distal colon. Therefore, an improvement in the dysbiosis observed in both saliva and intestine [120,121,122,123,124,125,126,127,128,129] is expected in patients supplemented with miraculin.

One disadvantage of clinical trials is the potential decrease in the number of patients, which may be further reduced due to dropouts throughout the study. However, the primary objective of the pilot clinical trial is to comprehensively assess various parameters affected in cancer patients, who are susceptible to improvement through regular consumption of the miraculin-based food supplement.

The outcomes of this pilot clinical trial are anticipated to demonstrate whether the regular consumption of a miraculin-based food supplement, whose active principle is the miracle berry extract DMB, has a positive effect on taste distortion and the nutritional status of malnourished cancer patients undergoing active antineoplastic treatment and to determine the dosage at which maximum benefits are achieved.

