#### 2.8.5. Diet

Inadequate dietary intake is an important factor involved in the weight loss and progressive functional decline associated with advanced cancer [69]. Reduced food intake is a well-established indicator of malnutrition that has strong validity. In this sense, less than or equal to 50% of energy requirements for more than one week, any reduction for more than 2 weeks, or any chronic gastrointestinal condition that adversely impacts food assimilation or absorption is considered reduced food intake or reduced assimilation, an etiologic criterion for malnutrition diagnosis [23].

Diet is collected in the 72 h food daily record at v1, v3, v4 and v5, allowing the transformation of food consumption into energy intake, water, macronutrient intake (proteins, fats (total fat, saturated (SFAs), monounsaturated (MUFAs) and polyunsaturated fatty acids (PUFAs), carbohydrates, fiber, and micronutrient intake (vitamins and minerals)). From this information, it is possible to calculate the caloric and lipid profile as well as the coverage of the recommended intakes of the population. Obtained data are to be evaluated using the European Food Safety Authority dietary reference values [70] and the Nutritional Objectives of the Consensus Document of the Spanish Community Nutrition Society [71]. If food intake does not meet energy requirements, a high-calorie, high-protein oral nutrition supplement with fiber, EPA, DHA, beta-glucans, and enriched in L-leucine (no added sugars) will be prescribed.

Dietary habits, diversity and variety will be measured using a quantitative FFQ. To evaluate the overall dietary habits, the consumption frequency of all food items will be categorized as meeting or not meeting the criteria of the dietary guidelines for the Spanish population [72], the food pyramid for the Spanish population [73], and the nutrition goals for the Spanish population [71].

Malnourished cancer patients with taste distortion and consuming the miraculin-based food supplement are expected to improve their dietary intake from baseline (v0) to the end of the intervention (v5). The mean of the difference between intake and food frequency found between these visits will be statistically compared with those found in the rest of the treatments. The evolution of diet will also be evaluated through the different intervention visits where it will be measured (v1, v3, v4, and v5).

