#### 2.8.10. Specialized Biochemical Parameters

##### Essential Fatty Acids and Polyunsaturated Fatty Acid Status

Malnutrition occurs frequently in cancer patients due to their oncological process and the treatments received, such as surgery, radiotherapy, or chemotherapy. The status of essential fatty acids (EFAs), linoleic acid (LA) (18:2 *n*-6) and α-linolenic acid (LNA) (18:3 *n*-3), as well as their long-chain polyunsaturated derivatives (LC-PUFAs), especially arachidonic acid (AA) (20:4 *n*-6, eicosapentaenoic acid (EPA) (20:5 *n*-3), docosapentaenoic acid (DPA) (22:5 *n*-3), and docosahexaenoic acid (22:6 *n*-3) (DHA), is essential for cellular homeostasis and, in particular, for the maintenance of immune and anti-inflammatory capacity [88,89,90]. It is well known that the EFA and LC-PUFA profile in erythrocyte membranes provides an accurate estimate of body fatty acid status in both healthy subjects [91] and cancer patients [92,93]. In the latter, EFA and LC-PUFA status is altered, usually due to low EFA intake [94]. The improvement of dysgeusia by the miraculin-based food supplement should potentially lead to increased food intake and, therefore, to a substantial improvement in EFA and LC-PUFA status.

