#### 3.4.2. Food Daily Record

For the quantitative assessment of the intake of energy and nutrients, a daily food record is used, following the recommended guidelines [147]. Foods, drinks, dietary supplements and preparations consumed for three days (one of which must be a holiday) before the consultation are recorded. The information obtained is structured in mealtimes (breakfast, mid-morning, lunch, mid-afternoon, dinner, and other meal moments). Patients are asked about the meal place (home, work, restaurant, etc.), food consumption time, and time spent (start and end time meal is registered). Patients provide a detailed description of food consumption (ingredients, method of preparation, brands, type). Subjects are instructed to record the weight of the food consumed or, if this is not possible, to record household measurements (spoonfuls, cups, etc.). At each visit, all records are thoroughly reviewed by a nutritionist in the presence of the patient to ensure that the information collected was complete. To facilitate the process, the nutritionist uses the “Photo guide of common portion sizes of Spanish foods”, which includes 12 food groups, 204 foods commonly consumed by the Spanish population, and 944 photographs [148].

The energy and nutritional content of the foods and beverages consumed are calculated using DIAL software (Alce Ingeniería, Madrid, Spain https://www.alceingenieria.net/nutricion.htm, accessed on 1 October 2023).

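### A rise in erythrocyte EPA or DHA can come from the omega-3 formula prescribed for low intake, so it cannot be read, as section 6 reads any change, as improvement brought about by better taste and more food

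*Protocol article*

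**What the plan says.** Section 2.8.10 names EPA and DHA among the erythrocyte fatty acids of interest. It sets out a causal path in which relief of dysgeusia by the product "should potentially lead to increased food intake and, therefore, to a substantial improvement in EFA and LC-PUFA status". Section 6 returns to this outcome and states that, after 12 weeks of supplementation, "any change in the fatty acid profile would be indicative of improved nutritional status".

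The same patients may receive a second source of these fatty acids. Section 2.8.5 says: "If food intake does not meet energy requirements", then "a high-calorie, high-protein oral nutrition supplement with fiber, EPA, DHA, beta-glucans, and enriched in L-leucine (no added sugars) will be prescribed". Section 4.2.1 provides at visit 1, where needed, that "a polymeric, hypercaloric, and hyperproteic formula enriched in omega-3 fatty acids is prescribed depending on their energy requirements". The study tablets are handed over at that same visit.

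The food record in section 3.4.2 covers "Foods, drinks, dietary supplements and preparations consumed for three days". Section 2.8 compares the mean change in each secondary outcome across the three arms. Section 2.13 allows for covariates without naming them.

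**The concern.** The stated reading takes the fatty acid profile as a marker at the end of one chain: better taste, more food, better fatty acid status. The formula opens a second route to the same marker, and it is triggered by the opposite condition, namely too little food. A patient who does not respond to the product, goes on eating poorly and is given formula may show a rise in EPA and DHA. Under section 6 that patient counts as supporting the hypothesis. As worded, so does a patient in whom these fatty acids fall.

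The diet outcome has a related weakness. Because the record includes supplements, formula can enter the energy and nutrient totals that are meant to show patients eating more food.

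What is at stake is the mechanistic conclusion of a pilot whose results, under section 2.10, are to serve as the basis for sizing later efficacy studies.

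**Working it through.** The article gives no figure on this point, so there is none to reproduce. The check sets the passages side by side and then illustrates size under stated assumptions.

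**Step 1: what a rise in EPA or DHA can mean.**
- Route A (section 2.8.10): product, less dysgeusia, more food, better fatty acid status.
- Route B (sections 2.8.5 and 4.2.1): intake below requirements, formula with EPA and DHA, higher EPA and DHA.

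Both routes can raise the same two fatty acids. Route A needs more food and route B is set off by too little, so the rise alone does not tell them apart. This argument covers EPA and DHA only; the article does not say that the formula supplies linoleic, α-linolenic or arachidonic acid.

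**Step 2: within-arm change.** Where formula is prescribed at v1, it and the tablets start from the same visit. Change from v1 to v5 within an arm then contains both and cannot separate them.

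**Step 3: between-arm change.** Let *s* be the mean shift in EPA or DHA among formula users, in SD units, and Δ*u* the difference between two arms in the proportion using formula. The part of the between-arm difference that passes through formula is

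*s* × Δ*u*.

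The article gives neither input. Assume *s* from 0.5 to 2 SD and Δ*u* from 0.10 to 0.40:
- lowest: 0.5 × 0.10 = 0.05 SD
- middle: 1 × 0.25 = 0.25 SD
- highest: 2 × 0.40 = 0.80 SD

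It is zero if use is equal across arms. If the product raises intake and so lowers formula use in the active arms, this part works against the part that passes through food, and the total difference is diluted.

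**Step 4: can equal use be taken for granted?** Section 2.6 plans 10 patients per arm. Assume the same true probability of formula use in two arms. The exact binomial probability that the observed proportions differ by at least 25 percentage points is 0.220 at a true use of 30%, 0.263 at 50% and 0.220 at 70%. For the completers, Table 3 implies arms of 8, 6 and 7: women are 5/8 = 62.5%, 2/6 = 33.3% and 6/7 = 85.7%, and 13/21 = 61.9% agrees with section 5. For pairs of these arms the probability runs from 0.284 to 0.412. A gap of this kind is sampling variation and not bias. It does mean that formula use must be seen by arm before a fatty acid difference is explained.

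**The case against.** The strongest reply has four parts.

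- **The sentence is narrative in Expected Results and not a test rule.** The text just before it implies a direction, and deleting it alters no planned comparison. This is true and limits the weight of the point. It remains the published reading of a planned outcome, and it would mislead whoever follows it.
- **A patient whose membrane EPA rises on formula does have better fatty acid status.** This also stands. The fault lies in crediting the rise to food intake or to the product, which is what sections 2.8.10 and 6 do together.
- **Formula is offered in all blinded arms on the same criterion.** A reader might infer that the between-arm comparison is confounded, that its sign is reversed, or that chance differences in formula use create a false product effect. The documents do not support this. Formula use that the product changes lies downstream of treatment, so the comparison still estimates the product's effect under the trial's nutritional care. Chance differences are sampling error, which the test allows for. Reversal, or an effect on weight, would need figures on formula content and use that the article does not give. Much formula use may also start at v1, before the product can act, and be similar across arms.
- **Covariates and sensitivity analyses belong in the analysis plan.** Agreed, so the unnamed covariates are no finding in themselves. An analysis plan would not correct the sentence in section 6.

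**Conclusion.** The point holds in a limited form. The article reads any change in the erythrocyte profile as improvement and attributes improvement to taste and food, while its own co-intervention supplies EPA and DHA to patients who eat too little. A rise in EPA or DHA may therefore mark formula use and low food intake, and the wording sets no direction.

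The randomised comparison stays valid as a treatment-policy effect, possibly diluted. Neither it nor a within-arm change can by itself establish the pathway from taste through food intake to fatty acids.

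The size is unknown. The range of 0.05 to 0.80 SD rests wholly on assumed inputs and shows only that the contribution could be anywhere from negligible to large. The reach is also limited: mainly two fatty acids within one secondary outcome, plus the reading of energy and nutrient intake. Nothing in the article shows that the primary electrogustometry endpoint is affected.

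**What to change.** 1. Reword the sentence in section 6. State the expected direction for each fatty acid, and say that changes in EPA and DHA cannot be credited to food intake or to the product without accounting for formula use.
2. Report formula use by arm.
3. Present energy and nutrient intake from food only, alongside total intake.
4. Adjust the fatty acid models for formula prescribed at v1 before the first tablet. That prescription precedes any effect of the product, so it can serve as a baseline covariate.

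An analysis confined to patients who never received formula should be left out or labelled purely descriptive. It selects on something that happens after randomisation and that the product may change, and with 21 completers in three arms the groups would be very small.

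The cost is one coded field from records already kept and one covariate in small models. The food records cover only three days per visit, so they will not give total formula intake over the three months. No change is proposed to who receives formula or when.
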